### 7.1.3 Analysis windows

For visits after the baseline, statistical analyses by visit are performed based on the scheduled visits, and the visits outside the protocol will not be considered. Test results of unscheduled visits in the protocol will be listed.

### 7.1.4 Analysis software

All statistical analyses are performed by the statistical software SAS 9.4 or above.

### 7.1.5 Tables and listings

➤ **Tables**

Data is generally summarized by groups (SCTV01E and placebo), and groups are generally displayed in columns.

### ➤ Listings

Unless otherwise specified, all listings include group and participant numbers, and priority is given to presenting the original data in SDTM. The information in listings is generally sequenced by group, participant number, visit time, or other relevant time (e.g., AE onset time).

## 7.2 Participant distribution

The number of participants that are screened, randomized, and complete the study, and the number of participants in each analysis set are summarized; the reasons for early withdrawal are analyzed. The participants failing the screening, the participants withdrawing early, and the participants not enrolled in the analysis sets are listed, respectively.

The incidence of protocol deviations/violations is calculated by total and classification, respectively, and a list of protocol deviations/violations will be provided.

## 7.3 Demographic data and baseline characteristics

Demographic data and baseline characteristics will be analyzed based on FAS, PPE, PPE-14, and I-PPE.

The descriptive statistics of the following demographic data and baseline characteristics will be given separately for participants in each group:

- Demographic data (including age, sex, height, weight, BMI, ethnicity, and race);
- Clinical characteristics during the screening period (including whether the participant has history of COVID-19 infection, the time from the last infection to this vaccination (months), whether the COVID-19 vaccine has been vaccinated before enrollment, the time from the last previous dose to this vaccination (months), the vaccine type of the last previous dose, the number of doses vaccinated, the types of each dose of vaccine, rapid antigen test results, nucleic acid test results, HIV test results, stratification of anti-SARS-CoV-2 IgG antibody level, and anti-SARS-CoV-2 IgG antibody results);
- Follow-up time of cases (including follow-up time of cases on Day 7 after vaccination, follow-up time of cases on Day 14 after vaccination, and follow-up time of cases after vaccination);
- Baseline vital signs (including systolic blood pressure, diastolic blood pressure, respiratory rate, pulse, body temperature);
- Baseline physical examination (including general examination, head and neck, lymph nodes, skin, chest, abdomen, musculoskeletal system, and others).

Time from the last previous infection to this vaccination (months) = (Vaccination date - Last infection date + 1) / 30.4375; the time from the last previous dose to this vaccination (months) =

(Vaccination date - Last dose date + 1) / 30.4375.

The previous medications and vaccinations are coded according to WHO DD (Chinese version, 202209), and statistical description is performed on the number of previous medications/vaccinations, number of participants involved, and frequency of medications/vaccinations by ATC2 classification and drug name, respectively.

The past medical history is coded according to MedDRA (V25.1\_Chinese version), and statistical description is performed on the number of past medical history, number of participants involved, and frequency of past medical history by SOC and PT, respectively.

The demographic list, list of past medical history, list of COVID-19 infection history, list of COVID-19 vaccination history, physical examination list, list of vital signs, rapid antigen test list, nucleic acid test list, HIV test list, list of anti-SARS-CoV-2 IgG antibody, list of previous medications, and list of previous vaccinations are provided.

#### **7.4 Concomitant medications and vaccinations**

Concomitant medications and vaccinations will be analyzed based on SS.

The concomitant medications and vaccinations are coded according to WHO DD (Chinese version, 202209), and statistical description is performed on the number of concomitant medications/vaccinations, number of participants involved, and frequency of medications/vaccinations by ATC2 classification and drug name, respectively.

A list of concomitant medications and a list of concomitant vaccinations are provided.

#### **7.5 Study hypotheses**

The lower limit of the two-sided 95% confidence interval (i.e., one-sided 97.5% confidence interval) of the protective efficacy (VE) of the vaccine against first occurrence of symptomatic infection of SARS-CoV-2 after 7 days post vaccination of 1 dose of Recombinant S-Trimer Protein Subunit (Alpha/Beta/Delta/Omicron Variant) Vaccine for SARS-CoV-2 (SCTV01E, COVID-19 vaccine) versus 1 dose of normal saline in participants aged  $\geq 18$  years is  $> 30\%$ . The following hypothesis tests are considered:

Null hypothesis  $H_0$ :  $VE \leq 30\%$ ;

Alternative hypothesis  $H_1$ :  $VE > 30\%$ .

#### **7.6 Efficacy evaluation**

##### **7.6.1 Primary efficacy evaluation**

✧ **Protective efficacy of the study vaccine against symptomatic infection of SARS-CoV-2 after 7 days post vaccination ( $\geq 8$  days) versus placebo**

The Cox proportional hazards model is used to statistically analyze the protective efficacy of the study vaccine against symptomatic infection of SARS-CoV-2 after 7 days post-vaccination, with the person-years at risk as the dependent variable and with the age (18–59 years,  $\geq 60$  years), the vaccine type of the last previous dose (inactivated, non-inactivated), and the group as fixed effects. The protection rate of the vaccine and its 95% confidence interval are calculated according to the model. Events that coincide in time are handled based on the Efron method. If the model reaches convergence, the stratification factor of the vaccine type of the last previous dose will be removed from the model first; if the model still converges, the age stratification factor will be further removed.

Person-years at risk of the primary endpoints = (End/censored time of valid case surveillance period - Vaccination time - 7) / 365.25; where, the end/censored time of valid case surveillance period is calculated according to the following rules:

- For those who have symptoms and are diagnosed with COVID-19 before the data cut-off date, the end time is the start date of the first symptom (first onset date) of the target event or the date of the positive result for antigen or nucleic acid tests corresponding to the event, whichever comes earlier;
- For those with positive results of rapid antigen and/or laboratory RT-PCR tests post vaccination before the data cut-off date, but not diagnosed with the target event, the censored time is the earlier of the sampling dates corresponding to the positive results for antigen and RT-PCR tests;
- For those with negative results of rapid antigen and/or laboratory RT-PCR test post vaccination before the data cut-off date, but not diagnosed with the target event, the censored time is the last follow-up date of the case surveillance;
- For those vaccinated with other COVID-19 vaccines before the data cut-off date, the censored time is the date of first vaccination with other COVID-19 vaccines; those diagnosed with target events after vaccination with other COVID-19 vaccines are not included in the case count.

The Kaplan-Meier curve for incidence of symptomatic COVID-19 after Day 7 post vaccination is plotted.

The primary protective efficacy analysis will be based on PPE. In addition, the sensitivity analysis will be performed with the following methods for the primary protective efficacy:

**Sensitivity analysis 1 (vaccine protection rate analysis based on exact Poisson regression model):** By the exact Poisson regression model, statistical analysis of the protective efficacy of the study vaccine against symptomatic infection of SARS-CoV-2 starting 7 days post vaccination is

performed. The vaccine protection rate based on person-year incidence rate and its 95% confidence interval are estimated according to the model. Poisson regression model is constructed with the number of cases as the dependent variable, the age (18–59 years,  $\geq 60$  years), the vaccine type of the last previous dose (inactivated, non-inactivated), and the group as fixed effects, and person-years at risk as the offset, and the log link function is employed.

**Sensitivity analysis 2 (vaccine protection rate analysis based on Cox model not including stratification factors):** The Cox proportional hazards model is used to statistically analyze the protective efficacy of the study vaccine against symptomatic infection of SARS-CoV-2 starting 7 days post vaccination, with the person-years at risk as the dependent variable, and the group as the fixed effect. The protection rate of the vaccine and its 95% confidence interval are calculated according to the model.

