| Study Design | 
SCT had initiated several clinical trials to evaluate the safety and immunogenicity of SCTV01E and SCTV01C, including one Phase III immunogenicity trial for SCTV01E and SCTV01C and three Phase I/II trials for SCTV01C. SCTV01E and SCTV01C were manufactured by the same platform, sharing the same process, similar molecular characteristics and clinical dosage, therefore, these trials provide sufficient supportive safety and immunogenicity clinical data prior to the start of this Phase III trial for SCTV01E. The details of these trials are summarized in the investigator's brochure.
 
The dose strength of SCTV01E is 30<math>\mu</math>g (5/5/5/15<math>\mu</math>g for TM22/TM23/TM28/TM41)/dose based on the nonclinical and clinical study of SCTV01E and SCTV01C.
 
The study is a randomized, double-blind, placebo-controlled Phase III study. It will evaluate the protective efficacy and safety of SCTV01E against COVID-19 in participants who were previously vaccinated with primary series of COVID-19 vaccines and /or received booster vaccination.
 
The study design is shown in Figure 1.
 
Approximately 10,000 participants who were previously vaccinated with the primary series of COVID-19 vaccine and/or received booster
 |

vaccination and aged  $\geq 18$  years old will be enrolled. The exact number of participants enrolled in the study will depend on the infection rate of COVID-19 infection at the time of enrollment and the true vaccine efficacy of SCTV01E. If the attack rate is much higher, case accrual would be expected to be more rapid, enabling the study's primary endpoint to be evaluated much sooner, and the actual enrolled sample size may be less than planned.

A percentage of 5%~10% participants in the full analysis set will be set for both immunogenicity test and efficacy evaluation. (No limitation for the type of COVID-19 vaccine previously received or age ranges).

Participants will be randomly assigned to receive one dose of SCTV01E or placebo (normal saline) in a ratio of 1:1 on Day 0.

Participants are stratified by age (18-59 years,  $\geq 60$  years), the type of the last dose of COVID-19 vaccine previously received (inactivate, non-inactive) and region (study site).

Participants aged between 59 years to less than 60 years old will be taken as 59 years old;

[figure not shown]

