| Inclusion Criteria | 
Participants are eligible to be included in the study only if the following conditions are met:
 
 
1. Male or female aged <math>\geq 18</math> years old when signing ICF (the specific age range depends on the authorized age range by the local regulatory authority);
 
2. Participants who were vaccinated with the primary series COVID-19 vaccine and/or received booster vaccination, and the interval between the last dose of COVID-19 vaccine and screening is 6-24 months;
 
3. The participant and/or his/her legal guardian and/or his entrusted person can sign written ICF, and can fully understand the trial procedure, the risk of participating in the trial, and other interventions that can be selected if they do not participate in the trial;
 
4. The baseline SARS-CoV-2 anti-Spike IgG will be measured at the screening period which should be lower than 338BAU/mL. It is aimed to recruit participants who are susceptible to SARS-CoV-2 infection (excluding the participants with baseline SARS-CoV-2 anti-Spike IgG <math>\geq 338</math>BAU/mL, who are highly associated with recent infection or in a recovery stage from SARS-CoV-2 infection). Most importantly, the upper limit was based on data obtained from previous studies (phase I/II). However, we may make adjustments to the upper limit of IgG test results at screening depending on the real situation; (e.g., in regions with low incidence of SARS-CoV-2 infection, this criteria may be adjusted or not be applied, if the number of participants exceeding this threshold reaches a certain proportion, the participants will be restricted to enroll according to
 
 |

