#### **Statistical analysis methods:**

##### **Efficacy analysis**

Analysis of the primary endpoint will be performed based on PPE.

Primary endpoint: The vaccine efficacy will be estimated with 1-HR using a Cox proportional hazard regression model with separate baseline strata of age (18-59 years,  $\geq 60$  years) and the type of the last dose of COVID-19 vaccine previously received (inactive, non-inactive). Events that coincide in time will be processed based on the Efron method.

Subgroup analysis of the primary efficacy endpoint will be performed to assess the consistency of vaccine efficacy, such as different ages (18-59 years,  $\geq 60$  years), and the type of the last dose of COVID-19 vaccine previously received (inactive, non-inactive).

Details of the sensitivity analysis are described in section 11.4.4.

Similar statistical analysis model will be applied to VE assessment for both the primary endpoint and second endpoints.

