**Immunogenicity evaluation:** Blood samples will be collected on Day 0 (pre-vaccination), Day 14 and Day 28 from participants in the immunogenicity subgroup (approximately 5%–10% of randomized participants), of which 200 participants need to undergo additional scheduled sampling on Day 7, Day 90 and other longer periods (detailed in the visit flow chart of the protocol) for the detection of SARS-CoV-2 (including mutant strains and mutant subtype) neutralizing antibody.

**Safety evaluation:** All participants will be observed at the study site for at least 30 minutes after the study intervention. Information is collected through a combination of active surveillance and spontaneous reporting. Solicited adverse events (AEs) within 7 days after vaccination and unsolicited AEs within 28 days after vaccination will be collected via vaccination record cards (VRCs). Serious adverse events (SAEs) and adverse events of special interest (AESIs) will be collected through active surveillance until the participant completes (or withdraws early from) the study.

This study will be conducted by Guizhou Center for Disease Control and Prevention, Sichuan Center for Disease Control and Prevention, and Hunan Provincial Center for Disease Control and Prevention.

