## 4.2 Randomization

This clinical trial is a randomized and double-blind Phase III clinical trial. Participants will be randomized to the study vaccine group or the placebo group at a ratio of 1:1. To maintain relative balance between groups, participants will be stratified and randomized by age (18–59 years,  $\geq 60$  years), vaccine type of the last previous dose (inactivated, non-inactivated), and region (study site). Blind codes for participant randomization and blind codes for drug numbers will be generated and maintained by a third party.

Participants eligible for screening will be randomized by the Interactive Web Response System (IWRS) and vaccinated according to random numbers. For participants who withdraw from the study for any reason after randomization, regardless of whether they are administrated with the study

vaccine or not, their random numbers will be retained, and they shall not participate in the study again.

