### 4.3 Sample size

After the adjustment of Beijing epidemic prevention and control policy, the protective efficacy of SCTV01E is between 70% and 77% in the real-world study. Therefore, assuming a protective efficacy (VE) of 70% (Hazard Ratio = 0.3) for the PPE population (as defined in the Analysis Set section) 7 days post-vaccination, in the condition of 59 cases, there is approximately 90% power to reject the null hypothesis  $H_0$  at a one-sided Type I error level of 0.025. The following assumption will be considered for sample size estimation and approximately 10000 participants (adjusted for actual infection rates) will be included. The final number of participants enrolled depends on the actual infection rate and the cumulative number of COVID-19 events. Of these participants, 5%–10% will be included in the immunogenicity subgroup.

- In the control group, the symptomatic infection of SARS-CoV-2 within 1 month is about 1.5%.
- The dropout rate during the study is about 10%.
- Approximately 15% of participants could not be included in the assessment of the number of events after 7 days because they are PCR positive at baseline or have an infection within 0–7 days after vaccination.

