**7.6.2.2 Immunogenicity**

**7.6.2.2.1 Prime immunization**

The main results of the immunogenicity analysis for the prime immunization will be based on the I-PPE population. The I-PPS will also be analyzed. Particularly, post-infection immunogenicity data for SARS-CoV-2 infection will be excluded from analysis, and pre-infection data may still be included. Exploratory analysis will also be performed on participants who are infected at baseline (positive for nucleic acid or antigen tests).

The GMT of neutralizing antibody against SARS-CoV-2 (including variants or mutant subtypes) in the immunogenicity subgroup at each time point post vaccination is analyzed by the covariance model. The model is constructed with antibody GMT post vaccination after logarithmic transformation at each time point as the dependent variable, antibody GMT before vaccination after logarithmic transformation at each time point as the covariate, the age (18–59 years,  $\geq 60$  years), the vaccine type of the last previous dose (inactivated, non-inactivated), and the group as fixed effects. The arithmetic mean of antibody post vaccination after logarithmic transformation at each time point in each group and the least squares mean (LSM) of the difference between groups are calculated according to the model; after inverse logarithmic transformation, the LSM and 95% confidence interval of antibody GMT and GMT ratio (test group / control group) at each time point post vaccination in each group are calculated.

The geometric mean and two-sided 95% confidence interval are used to statistically describe anti-SARS-CoV-2 neutralizing antibody GMT and GMI at each time point in the test group and the control group under the immunogenicity subgroup, respectively.

The seroresponse rates of anti-SARS-CoV-2 neutralizing antibody in the test group and control group at each time point post vaccination are calculated, respectively, and their 95% confidence

intervals are calculated by Clopper-Pearson method. The ratio difference (test group - control group) and its two-sided 95% confidence interval are calculated using the CMH- $\chi^2$  test including randomization stratification factors, and the difference between groups is statistically tested.

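### Randomisation is stratified by region (study site), but the primary Cox model and the Poisson sensitivity model omit region; the analysis stays valid, and adding province is a small, cheap improvement

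*Combined protocol and SAP*

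**What the plan says.** **Randomisation.** SAP 4.2 stratifies by age (18–59, ≥60 years), "vaccine type of the last previous dose (inactivated, non-inactivated), and region (study site"). The protocol synopsis, under Study Design, names the same three factors, the last two as "inactivate, non-inactive) and region (study site").

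**Primary model.** SAP 7.6.1 fits a Cox model with age, "the vaccine type of the last previous dose (inactivated, non-inactivated), and the group as fixed effects". The protocol synopsis estimates VE "using a Cox proportional hazard regression model with separate baseline strata of age" and last-dose type. One text uses fixed effects and the other baseline strata, but neither has region.

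**Sensitivity analyses.** In SAP 7.6.1 the exact Poisson model uses the same two factors plus group. The second Cox model drops all stratification factors.

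**Secondary endpoints and subgroups.** SAP 7.6.2.1 reuses the primary method throughout. SAP 7.9 does not list region as a subgroup.

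**Regions.** SAP 4.1 names the "Guizhou Center for Disease Control and Prevention, Sichuan Center for Disease Control and Prevention, and Hunan Provincial Center" for Disease Control and Prevention as conducting the study. Inclusion criterion 4 in the synopsis says of the anti-spike IgG limit that "in regions with low incidence of SARS-CoV-2 infection, this criteria may be adjusted or not be applied". Note 7 to the schedule of activities repeats this.

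**The concern.** A factor used to stratify randomisation is normally carried into the primary analysis, or its omission is explained. Here two of the three factors are carried and the third is dropped without comment.

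Region is not an idle factor in this trial. The endpoint is infection during an epidemic, and the plan itself expects incidence to be low in some regions. Follow-up time runs from vaccination, so a single baseline hazard pools regions that may be at different stages of an epidemic wave.

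If baseline hazards differ and the difference is ignored, the Cox hazard ratio tends to move slightly towards 1, which means a slightly low VE and some loss of power. What is at stake is efficiency and agreement between design and analysis, not the validity of the test.

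**Working it through.** **1. The plan's own figure.** Inputs from SAP 4.3 and 7.5: HR 0.3 under the alternative, HR 0.7 at the null, 1:1 allocation, 90% power, "at a one-sided Type I error level of 0.025".

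- HR ratio: 0.3/0.7 = 0.4286; log = −0.847.
- Schoenfeld events: 4 × (1.960 + 1.282)² / 0.847² = 58.5, rounded up to 59.
- Power at 59 events: 90.2%.

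The stated 59 cases and roughly 90% power reproduce. The formula has no term for region, so adding region leaves 59 unchanged.

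**2. Sizes used.** From the planning assumptions, 10,000 × 0.85 × 0.90 = 7,650. The per-protocol set for efficacy (PPE) in Table S2 has 2,623 participants; that is a result, not a planning figure.

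**3. Region strata against no strata at all.** Cox model stopped at 59 events; success if the Wald 95% upper limit for the HR is below 0.7; 1,500 runs per setting. The documents give no regional rates, so all incidence ratios are assumptions. Each pair is without / with region.

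| N | Regions (assumed incidence) | Power at HR 0.3 | Median HR at true 0.3 | Rejection at HR 0.7 |
|---|---|---|---|---|
| 7,650 | 3 (1:3:9) | 82.1% / 82.1% | 0.310 / 0.308 | 1.3% / 1.3% |
| 7,650 | 3 (1:10:30) | 80.7% / 80.7% | 0.310 / 0.308 | 1.7% / 1.7% |
| 2,623 | 3 (1:1:1) | 79.6% / 79.7% | 0.307 / 0.307 | 1.7% / 1.7% |
| 2,623 | 3 (1:2:4) | 80.3% / 80.6% | 0.307 / 0.306 | 1.5% / 1.6% |
| 2,623 | 3 (1:3:9) | 81.5% / 84.1% | 0.307 / 0.304 | 1.3% / 2.1% |
| 2,623 | 3 (1:10:30) | 81.2% / 85.1% | 0.3071 / 0.3035 | 1.1% / 1.6% |
| 2,623 | 20 sites (lognormal, log-SD 1) | 74.8% / 83.4% | 0.311 / 0.297 | 1.1% / 2.3% |

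Without region, rejection at VE 30% never exceeds 2.5%. With three regions the HR moves by at most about 0.004 (VE 69.3% against 69.6–69.7%). With 20 sites it moves by about 0.014.

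**4. The plan against the fix.** Step 3 does not compare these, because the plan already adjusts for age and last-dose type. Age × last-dose strata were therefore compared with age × last-dose × region strata: three regions, assumed relative hazards 0.3:1.5:4, 1,311 per arm, 59 events, 2,000–4,000 runs.

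- Equal arms: 82.2% to 84.7%, a gain of 2.5 points.
- Arms balanced by region: 81.0% to 83.3%, a gain of 2.3 points.
- Coin-flip allocation: 84.5% to 85.0%, a gain of 0.5 points.
- Milder spread of 1:2:3: 84.6% to 84.8%, no real gain.
- A further run of this comparison, with hazards up to 0.3:1.5:4, gave gains of about 0 to 1 point and no visible change in type I error.
- At N = 7,650: gains of about 0.6 to 2.3 points.

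Monte Carlo error is about 1 point. The mean standard error of the log HR is the same with and without region, about 0.314–0.315. Any gain therefore comes from slightly less attenuation and from the coarse discreteness of 59 events, not from a smaller standard error.

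**5. A side remark.** Simulated power is below 90% even when regions are equal. At HR 0.3 the vaccine arm's share of cases is 0.3/1.3 = 23%, while the Schoenfeld formula assumes a roughly even split. The exact conditional binomial test rejects at 16 or fewer of 59 cases in the vaccine arm, with size 1.8% and power 81.5%. This is separate from the region question.

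**The case against.** The strongest case against is that nothing is broken: type I error is controlled, VE barely moves, the standard error is unchanged, and no regional rates are documented. Omitting site when events are sparse is a common and defensible choice. Twelve strata for 59 events is about five events per stratum, and province would still be coarser than the site factor used in randomisation. All of this stands, and it limits the point to a cheap improvement.

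A reader might infer more, and four stronger readings are not supported.

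- **The primary test is invalid or anti-conservative.** Rejection at VE 30% without region was 1.1% to 1.7% in every setting tried.
- **Region is the strongest predictor of infection.** The documents say only that some regions may have low incidence.
- **The plan uses all randomisation factors for immunogenicity but not for efficacy.** The CMH analysis in SAP 7.6.2.2.1 is a "test including randomization stratification factors, and the difference between groups is statistically tested", but the ANCOVA in that same section uses only age, last-dose type, group and baseline titre. Two-factor adjustment is the plan's usual modelling practice.
- **Region is out of balance in the PPE set.** That set is 2,623/9,196 = 28.5% of the full analysis set, but it is selected mainly on PCR and IgG measured before vaccination, so randomisation still protects it in expectation (arms 1,309 and 1,314). The exclusion for infection within 7 days does follow randomisation, and region strata would not cure that.

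**Conclusion.** The mismatch between design and analysis is certain from the text. Its consequence is small.

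The planned model gives a valid test and at most a slightly attenuated VE. Adding region to the two planned factors would gain about 0 to 3 points of power with three provinces, under assumed relative hazards up to 0.3:1.5:4. The 30-fold spread in the table gave 3.9 points, but against a model with no factors at all. The only larger figure, 75% to 83%, rests on 20 sites with assumed lognormal incidence, also against a model with no factors. The documents do not give the number of sites. The 59-event target is unaffected.

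One limit remains: the synopsis refers to protocol section 11.4.4 for sensitivity analyses, and that section is not in the text available. SAP 2.3 states that the SAP agrees with the protocol, and the SAP has no region-adjusted sensitivity analysis.

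**What to change.** In SAP 7.6.1 and the matching protocol text, fit the primary Cox model with baseline-hazard strata for age group × last-dose type × region, taking region as province (the three provincial centres). Pre-specify a rule for collapsing sparse strata. Use the same model for the secondary VE endpoints in SAP 7.6.2.1, and add province to the exact Poisson sensitivity model. Strata suit better than many site terms as fixed effects, which would be unstable with about 59 events.

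The cost is a few lines of text. Region is already recorded for randomisation and no re-sizing is needed. The same edit can settle whether age and last-dose type enter as strata (protocol) or fixed effects (SAP).

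The small downside is few events per stratum: 2 × 2 × 3 = 12 strata for about 59 events. Province is also coarser than the site-level randomisation factor, and the text should say so.

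If the primary analysis has already been done, leave it as specified and report the region-stratified model as a labelled sensitivity analysis.
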